### **5.3.1 Screening Procedures**

See section 5.1

### 5.3.2 Recruitment, Enrollment and Retention

Potential subjects will be identified from community advertisements and referrals, primarily from social media advertisements. If we encounter difficulty with recruitment to meet planned targets, we may engage a professional clinical trial recruitment company, such as Build Clinical, to support our recruitment.

All potential participants from any source will be directed to complete a brief screening survey on a secure online platform (e.g. REDCap) to screen out people with common exclusions (e.g. age, location, current DBT psychotherapy, MRI exclusions).

People who may be eligible after the screening survey will be invited to participate in a 15-20 min phone call with a [name] lab staff member to identify further common exclusion criteria, including some questions about clinical symptoms. Questions will include demographics, MRI safety and comfort rule-outs, and clinical symptoms to determine likelihood of meeting BPD criteria at full screen.

**We will request a waiver of HIPAA authorization for these first two screening steps (for recruitment only), as subjects will be screened in these two steps before the first meeting when the consent process and signing of consent paperwork occurs.**

People who may be eligible after phone screen will be invited to participate in a first full screening visit to be conducted by the [name] team (for participants at both sites). Those who agree to schedule a visit will be emailed an e-consent form from REDCap which they can review prior to their visit.

If a potential participant joins a first screening visit (always a live meeting, usually remote, with a [name] lab staff member), the first step will be the consent process, including a review of study overview and goals, study procedures, study risks and benefits, confidentiality, economic considerations, and in-person expectations regarding infection control for MRI days. Then the participant will have unlimited time to review the e-consent form and ask questions. Only if they decide to sign and submit the form does the visit proceed.

## 5.4 Statistical Method

### 5.4.1 Statistical Design, Sample size determination, and Planned Analyses

*Data Preparation* Data will be examined for outliers, non-normal distributions, and non-linear associations. Preliminary analyses will examine potential covariates including site, age, sex, clinical variables, and head motion. We will explore the presence of group effects (and time effects when appropriate) across individual covariates or combined factors across multiple covariates using a liberal  $p < .05$  uncorrected threshold and include any suprathreshold variable as control covariate in subsequent analyses. Detailed information regarding psychiatric service use (e.g., therapy, medication, unplanned mental health service use) will be assessed to test whether this differentially impacts (or is affected by) change in our neural targets. We will also explore baseline symptoms as a potential covariate in the analyses. Conclusions will primarily be based on effect sizes with 95% confidence intervals rather than statistical significance to maximize reproducibility. Based on our prior studies, we estimate ~30% attrition/data loss. We have planned for adequate initial recruitment to anticipate complete data to include 124 subjects.

### **1. Target Engagement: DBT with mbNF will change resting-state DMN connectivity toward a more mindful brain state.**

We will test if mbNF leads to larger changes than control-NF (medium effect-size  $d \geq 0.5$ ) in at least one of our two DMN connectivity targets. We will calculate within-subject change from pre- to post-NF, then use one-tailed t-tests (mbNF vs. controlNF) to test our hypothesis that mbNF will lead to larger change by decreasing within-DMN connectivity and/or increasing DMN-FPCN anticorrelation. This effect size is in line with our prior mbNF research in other patient groups (where we saw effect sizes of  $d=0.7$  to  $d=0.91$ ).

**2. Our primary clinical outcome is change in BPD symptom severity (BSL23 survey score) in the full study sample (62/group). Our secondary outcome is change in current-moment mindfulness (SMS score).** For each outcome, we will test the hypothesis that mbNF+DBTsg will decrease score more than control-NF+DBTsg from baseline (pre-NF) to primary endpoint (DBTsg week 16) using a linear mixed regression model with group (between-subject) x time (within-subject) interaction. Based on previous work, we expect significant medium-large effects. Correlation between repeated observations within-subject will be modeled with structured variance-covariance and/or random subject effects. The best-fitting model will be chosen based on information criteria. Least-square (LS) means will be compared and plotted post-hoc to examine significant effects. Power Analysis: Using G\*power, we estimate achieving 80% power to detect small effects ( $f=0.15$ ) with 62 subjects in each of two groups, two timepoints,  $p=0.05$ , correlation among measures 0.3, and sphericity assumed.

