### **4. (exploratory): How long do neural and symptom changes last after mbNF + DBT?**

We hypothesize that changes in neural connectivity and decreases in BPD symptom severity will last for several months after mbNF. We will explore the durability of observed changes using linear mixed-effects models testing for group (mbNF vs. controlNF) x timepoint (pre-NF to post- NF, 5 timepoints during DBTsg, and at 1- and 2-month post-DBT follow-up timepoints) in symptom change (primary: BSL23; secondary: SMS). Models will include a random effect for subject and fixed-effect covariates (e.g., age, sex, site, baseline symptoms).

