### 5.4.2 Analysis of Subject Characteristics

*Sex as a Biological Variable* The extent of sex differences in the neurobiology and behavioral expression of BPD remain unclear. We will test sex differences in all variables as well as sex as a moderator of key predictors. Given well-established sex differences in the frequency of patients being given the BPD diagnosis and presentation for mental healthcare (despite likely-similar community prevalence), we expect that our sample will be ~80% female. Although not our main aim, we will provide important preliminary results regarding sex differences in response to mbNF.

*Site Differences* Though we aim to minimize site differences in sociodemographic factors, we will probe potential differences and control for these in analyses. To further control for potential differences between the two sites, we will implement ComBat harmonization to remove site-related variance in connectivity measures. ComBat has been shown to facilitate reliable and efficient analysis, accounting for non-biological, scanner-specific sources of variability, in multi-site fMRI neuroimaging studies. Additionally, all analyses will include a main effect of site, and we will examine potential first-order site x time and site x group x time interactions.

To further understand effects for the neural and clinical targets, we will control for key covariates (e.g., age, sex, site, head motion, clinical and demographic variables that differ between groups), and explore the impacts of mbNF vs. controlNF on the use of mindfulness skills and DBT skills from each module in daily life, DBTsg group attendance, and use of mental healthcare resources outside the study. We will also relate acceptability and tolerability data from program evaluation to attendance and dropout data.

As an exploratory analysis of broader modulation within the DMN, we will test within-DMN connectivity between other common nodes, i.e. posteromedial cortex, angular gyrus, lateral and medial temporal cortex. Furthermore, to explore the spatial specificity of our findings, we will perform this model on DMN connectivity voxel-wise (mPFC seed) across the brain using Threshold Free Cluster Enhancement (TFCE) for multiple comparisons correction.

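### The BSL23, SMS and connectivity tests are unadjusted change-score comparisons; adjusting for the pre-NF value would cut the variance to 0.65 at the protocol's own correlation of 0.3, at no cost in data

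*Protocol*

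**What the plan says.** **Clinical outcomes.** Protocol section 5.4.1 item 2 compares the arms on BSL23 (primary) and SMS (secondary) "from baseline (pre-NF) to primary endpoint (DBTsg week 16", "using a linear mixed regression model with group (between-subject) x time (within-subject) interaction". No common-baseline constraint is stated. The covariance structure (a structured matrix, random subject effects, or both) is left to information criteria. The power statement is "we estimate achieving 80% power to detect small effects ( $f=0.15", "with 62 subjects in each of two groups, two timepoints", at the 0.05 level with a correlation of 0.3.

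**Connectivity.** Item 1 reads "We will calculate within-subject change from pre- to post-NF, then use one-tailed t-tests (mbNF vs. controlNF". Section 5.4.3 applies the same test to the GO decision with 26 per group and a threshold of d = 0.5.

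**Baseline.** Under Data Preparation in section 5.4.1: "We will also explore baseline symptoms as a potential covariate in the analyses". For the exploratory durability analysis (item 4), where pre-NF is itself one of the timepoints: "Models will include a random effect for subject and fixed-effect covariates (e.g., age, sex, site, baseline symptoms". Baseline connectivity is nowhere named as a covariate.

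**Site.** Section 5.4.2 states that "all analyses will include a main effect of site", and also plans site x time terms and ComBat harmonization of connectivity.

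**The concern.** With pre-NF as a response and a free group difference at baseline, the two-timepoint interaction is the difference between arms in mean change. This subtracts the whole baseline value, whereas at a correlation of 0.3 and equal variances the best-predicting slope is 0.3. Because participants are randomized within site, the arms differ at pre-NF only by chance, so adjusting for the pre-NF value is valid and more precise. The protocol bases its conclusions mainly on effect sizes with 95% confidence intervals, so precision is what it values most.

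The remedy it mentions, baseline symptoms as a covariate, does not help in a model that already has pre-NF as an outcome, and under some specifications it makes the standard error too small. For connectivity the relevant covariate is not named at all, and the named test has no place for site.

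**Working it through.** **Inputs.** From section 5.4.1 item 2: 62 per group, two timepoints, f = 0.15, alpha 0.05, correlation rho = 0.3. From section 5.4.3: 26 per group, d = 0.5, one-tailed; I take alpha as 0.05. The documents give no correlation for connectivity, so 0.3, 0.5 and 0.7 are assumptions.

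**1. The plan's own figure.** For the within-between interaction, lambda = f² × N × m / (1 − rho) = 0.0225 × 124 × 2 / 0.7 = 7.97. With F(1, 122) the power is 0.79986. The stated 80% reproduces.

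**2. The same test as a change score.** f = 0.15 corresponds to a difference in change of 4 × 0.15 = 0.60 SD. The SD of change is √(2 × (1 − 0.3)) = √1.40 = 1.183, so d on the change score is 0.60 / 1.183 = 0.507. A two-sample t-test with 62 per group again gives 0.800.

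**3. Baseline adjustment.** The residual variance is 1 − rho² = 1 − 0.09 = 0.91 (SD 0.954). The ratio to the change score is (1 − rho²) / (2(1 − rho)) = (1 + rho)/2.

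| rho | Variance, change | Variance, adjusted | Ratio | Planned-test N matching 124 adjusted |
|---|---|---|---|---|
| 0.3 | 1.40 | 0.91 | 0.65 | 124/0.65 ≈ 191 |
| 0.5 | 1.00 | 0.75 | 0.75 | 124/0.75 ≈ 165 |
| 0.7 | 0.60 | 0.51 | 0.85 | 124/0.85 ≈ 146 |

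At rho = 0.3, power at 0.60 SD rises from 0.800 to 0.935, and the difference detectable with 80% power falls from 0.60 to 0.48 SD. A week-16 comparison that ignores baseline altogether has variance 1.00, which also beats the planned contrast at this correlation.

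**4. Connectivity and GO.** One-tailed test, true d = 0.5 on the change score, per target:

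| Per group | Change-score t-test | ANCOVA, rho 0.3 / 0.5 / 0.7 (assumed) |
|---|---|---|
| 26 | 0.55 | 0.71 / 0.66 / 0.61 |
| 62 | 0.87 | 0.96 / 0.94 / 0.91 |

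**5. The pre-NF score as a main-effect covariate, two timepoints.** A subject-level main effect enters both timepoints equally and cancels from the interaction. In simulation the estimate with and without it agreed to about 1e-15. With a random intercept that cannot be negative, the covariance of the residuals after this covariate is −(1 − rho)²/4 = −0.1225, so the subject variance goes to zero. The model standard error is then 0.193 against a true value of 0.212 (ratio 0.908). Type I error in 5,000 null trials was 7.5% at rho 0.3, against 4.9% for the plain change-score test.

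**6. The same covariate with the nine timepoints of item 4** (pre-NF, post-NF, five during DBTsg, two at follow-up). In simulation with compound-symmetric data and a random intercept, the subject variance did not go to zero and rejection at rho 0.3 was 4.8%. The covariate gives no gain there, but no inflation was shown either.

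**The case against.** The group x time test is valid under randomization, matches a hypothesis about change, and has correctly stated power. The finer model specification is often left to the SAP. Section 5.4.4 plans imputation or weighting for missing data. Site effects that are purely additive cancel in a change score, and site x time terms and ComBat are also planned. All of this stands, so there is no error of validity or sample size here. It does not remove the point, because the protocol itself names the less efficient tests. ComBat also does not put a site term into a t-test.

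Four stronger readings are tempting but unsupported:

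- *Baseline is thrown away.* It is used, with its slope fixed at 1.
- *The covariate option inflates type I error.* This needs two timepoints, a random intercept that cannot be negative, and the pre-NF score as the covariate. Item 2 also allows a structured covariance; compound symmetry with a negative covariance gives a correct standard error. Section 5.1 lists a baseline measurement separate from the one before neurofeedback. The double use is written out only in the exploratory item 4, where inflation was not shown.
- *The 30% attrition cuts the 124 to about 87 (124 × 0.7).* Section 5.4.1 makes 124 the number with complete data, so this counts the loss twice.
- *The GO test loses the same third of its information.* The 0.65 rests on a correlation stated for the clinical power calculation; none is given for connectivity.

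**Conclusion.** The point holds as a loss of efficiency. At the protocol's own rho of 0.3, the planned BSL23/SMS contrast forgoes a 35% variance reduction, the difference between power of 0.80 and 0.935 at 0.60 SD. At rho 0.5 or 0.7 the reduction is 25% or 15%. These figures assume complete two-timepoint data and equal variances at the two times. For GO, power per target could rise from 0.55 to between 0.61 and 0.71 over the assumed correlations. The named baseline option leaves the interaction estimate unchanged and carries a conditional risk of a type I error of about 7% at rho 0.3. Separately, the two-sample t-tests as written conflict with the commitment to include site in all analyses. The change should be made, although the trial would remain valid without it.

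**What to change.** - **BSL23 and SMS:** use ANCOVA of the week-16 score on the pre-NF score, arm and site. Alternatively, use a mixed model with pre-NF as an outcome, pre-NF means constrained equal across arms, site and site x time, and the arm contrast taken at week 16.
- **Connectivity:** use ANCOVA of post-NF on pre-NF connectivity, arm and site. This also removes the conflict with section 5.4.2.
- **GO rule:** divide the adjusted difference by the SD of the change score, so that the threshold of d = 0.5 keeps its present meaning.
- **Covariates:** do not enter the pre-NF score as a main effect in any model where pre-NF is an outcome. Amend the Data Preparation text and item 4 accordingly.

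The cost is analysis wording only. No new data, visits or participants are needed, and the sample size can stay as it is.

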### **3. Target engagement will be related to decrease in BPD symptom severity in the mbNF sample, (n=62)**

We will use Pearson correlation to test the relationships between resting state DMN connectivity outcomes (pre- to post-NF change in within-DMN connectivity and DMN-FPCN anticorrelation) and BPD symptom severity (change in BSL23 score from pre-NF to primary endpoint). Power analysis: Using G\*power, we estimate achieving 80% power to detect small effects ( $r = 0.21$ ) with 124 subjects,  $\alpha 0.05$ .

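### The connectivity–symptom correlation is placed in the 62 mbNF participants but powered on 124, and r = 0.21 does not reach 80% power at either number

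*Protocol*

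**What the plan says.** Protocol section 5.4.1, item 3, carries the heading "Target engagement will be related to decrease in BPD symptom severity in the mbNF sample, (n=62"). The method is a Pearson correlation: "We will use Pearson correlation to test the relationships between resting state DMN connectivity outcomes" (change from before to after neurofeedback in each of the two connectivity measures) and the change in BSL23 from pre-NF to the week-16 endpoint. The power sentence in the same item reads "we estimate achieving 80% power to detect small effects ( $r = 0.21$ ) with 124 subjects", at alpha 0.05. It does not say whether the test is one- or two-sided.

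Three other statements bear on this:

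- Item 2 of the same section gives the trial size as "in the full study sample (62/group"), so 124 is the two arms combined. Section 4.3.2 agrees, with 31 completers per arm at each of two sites.
- The data-preparation paragraph of 5.4.1 says "we estimate ~30% attrition/data loss" and then "We have planned for adequate initial recruitment to anticipate complete data to include 124 subjects". So 124 is the number after losses, not the number recruited.
- Item 1 tests the same connectivity changes between arms with a stated direction: "then use one-tailed t-tests (mbNF vs. controlNF").

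**The concern.** The heading and the power sentence of one short item name different samples, and nothing in the item explains why an analysis of one arm is powered on both. Separately, the combination of 124 subjects, r = 0.21 and 80% power looks too favourable for a correlation.

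The mechanism of mbNF is part of the primary objective (section 3.2), and item 3 is the only analysis listed in 5.4.1 that links connectivity change to symptom change. A reader of the protocol would believe that an association explaining about 4% of the variance (0.21² = 0.044) is detectable with 80% power. The item also leaves open whether 62 or 124 participants will be analysed. These are different quantities: pooling the arms mixes the association within arms with any difference between arms.

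**Working it through.** **Inputs.** r = 0.21, alpha 0.05, target power 80% and N = 124 (item 3, power sentence); n = 62 (item 3, heading). Sidedness is not given, so both are tried. Each correlation is tested at 0.05, as stated.

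**Formula.** Fisher z: power = Φ( atanh(r) × √(n − 3) − z ), with z = 1.960 two-sided or 1.645 one-sided. atanh(0.21) = 0.2132.

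**The plan's own figure, n = 124.** √121 = 11, and 0.2132 × 11 = 2.345.

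- Two-sided: Φ(2.345 − 1.960) = Φ(0.385) = 65.0%.
- One-sided: Φ(2.345 − 1.645) = Φ(0.700) = 75.8%.

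The stated 80% is not reproduced.

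**The sample in the heading, n = 62.** √59 = 7.681, and 0.2132 × 7.681 = 1.637.

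- Two-sided: Φ(1.637 − 1.960) = Φ(−0.323) = 37.4%.
- One-sided: Φ(1.637 − 1.645) = Φ(−0.008) = 49.7%.

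**Check by other methods (power for r = 0.21).**

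| n, test | Fisher z | Exact distribution of r | Noncentral t | Simulation (100,000) |
|---|---|---|---|---|
| 62, two-sided | 37.4% | 37.8% | 38.4% | 37.6% |
| 62, one-sided | 49.7% | 50.3% | 51.1% | 50.2% |
| 124, two-sided | 65.0% | 65.3% | 66.0% | 65.3% |
| 124, one-sided | 75.8% | 76.2% | 76.8% | 75.9% |

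**Smallest r with 80% power.** r = tanh( (z + 0.842) / √(n − 3) ).

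- n = 62, two-sided: tanh(2.802 / 7.681) = 0.349 (0.340 to 0.349 across methods); r² about 12%.
- n = 62, one-sided: tanh(2.487 / 7.681) = 0.313 (0.304 to 0.313); r² about 10%.
- n = 124, two-sided: tanh(2.802 / 11) = 0.249 (0.246 to 0.249).
- n = 124, one-sided: tanh(2.487 / 11) = 0.222 (0.219 to 0.222).

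**Number needed for r = 0.21 at 80% power.** n = ( (z + 0.842) / 0.2132 )² + 3, which gives 176 two-sided and 140 one-sided (173 to 176 and 136 to 140 across methods).

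**Does this touch the main sample size?** Item 2 uses f = 0.15, two groups, two timepoints, correlation 0.3 and N = 124. The noncentrality is 0.15² × 124 × 2 / (1 − 0.3) = 7.97 on 1 and 122 degrees of freedom, which gives about 80%. That statement reproduces.

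**The case against.** **The miss may be small.** Item 1 tests the same connectivity changes one-tailed, so a one-sided correlation is a fair guess. At n = 124 the detectable r is then 0.22 against the stated 0.21. If 0.21 were rounded down from just under 0.215, the noncentral-t calculation gives 78.6%. This stands as far as it goes: on that reading the error is minor. But it contradicts the heading, and at n = 62 even the one-sided power is only about 50%.

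**Attrition might explain the figure.** 124 / 0.7 is about 178, and r = 0.21 has 80.7% power two-sided at 178. That is only a guess at the origin. The sentence says 124, and 124 is already the complete-data count.

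**A null result would not necessarily be misread.** Section 5.4.1 says conclusions will rest mainly on effect sizes with 95% confidence intervals. A wide interval at n = 62 would show the imprecision. This safeguard stands and limits the harm, but it does not make the stated power correct.

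**A stronger reading: the mechanism question cannot be answered.** A reader might infer that a correlation inside the treated arm ignores randomisation and so leaves the mechanism objective unaddressed. The protocol does not support that. Items 1 and 2 test the randomised contrast on connectivity and on BSL23, item 3 adds the link between them, and section 2.2 foresees testing mediation. A treated-arm correlation is weak causal evidence taken alone, but it is not taken alone here, and the form of any mediation model is commonly left to the analysis plan.

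**Conclusion.** The point holds in two parts. First, item 3 contradicts itself on its sample: the mbNF arm (62) in the heading, both arms (124) in the power sentence. Second, the claimed 80% power for r = 0.21 is not met on any reading. The shortfall is about 42 points two-sided or 30 points one-sided at n = 62, about 15 points two-sided at n = 124, and about 4 points one-sided at n = 124. The substantive defect is 62 against 124.

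This rests on a bivariate Pearson test at alpha 0.05, complete data in the named sample, and no adjustment for testing two connectivity measures.

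A reader might also infer that the trial as a whole is underpowered. Nothing here shows that: the power statement for the BSL23 comparison reproduces, and correcting item 3 does not by itself alter enrolment, randomisation, that analysis or the go/no-go rule in section 5.4.3.

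**What to change.** In section 5.4.1, item 3:

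1. Name one analysis sample and use it in both the heading and the power sentence.
2. State whether the test is one- or two-sided.
3. Restate the correlation detectable at 80% power in that sample: about 0.35 two-sided or 0.31 one-sided for n = 62; about 0.25 two-sided or 0.22 one-sided for n = 124.
4. If all 124 are used, change the heading and adjust the association for arm, so that it is not a mixture of between-arm and within-arm association.

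An arm-adjusted mediation analysis in all 124 would be a reasonable optional addition alongside the randomised contrasts in items 1 and 2. The figure of 0.25 must not be quoted as its power, because an indirect effect needs both paths. As an illustration, assume d = 0.5 for the arm effect on connectivity (the value in item 1), a within-arm correlation of 0.25, and two-sided 5% tests. The arm path has about Φ(0.5 × √31 − 1.98) = Φ(0.80) = 79% power and the second path about 80%. If the two are treated as independent, joint power is about 0.79 × 0.80 = 63%. It would need its own calculation.

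The cost is a change of wording and a less favourable stated detectable effect. No new data are needed.
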